### Statistical analysis

Data will be checked for normal distribution before applying the right type of parametric or non-parametric tests. First, descriptive statistics will be used to describe the two samples. Independent sample T-tests or appropriate non-parametric tests will be used to to determine the differences between the sport and non-sport group.

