#### Injuries and illness

The incidence and type of injury and illness of the participant at T0 and 3 months in retrospective will be filled out via a digital questionnaire and takes 5 min to complete. The injury density (ID) will be calculated per 1000 h of scheduled physical activity (van Mechelen et al. 1992).

Besides the retrospective registration, the injuries and illnesses will also be monitored longitudinal for 1 year, every 2 weeks. The parent and/or participant receives a short digital questionnaire of 5 simple questions, send by email and takes approximately 1 min to complete. If a question will be answered positively, there will be a telephone conversation with the child, young adult or parent, to detect the cause and severity to register the diagnosis of injury or illness. The researcher will register the injury by using a classification list. Only if the diagnosis remains unclear after the telephone conversation, a physical examination of a sports physician or a physical therapist will take place.

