## Sample size

The sample size of the HAYS-study is based on a study of Verschuren and Takken (2010). In this study children and adolescents with cerebral palsy had an average peak oxygen uptake of 42 ± 8.2 ml/kg/min. To prove a difference of 10 % between sporting or non-sporting subjects, with an alpha of 0.05 and bèta of 0.20 (power of 0.80) a sample size of 66 subjects per group is required. When taking a failure rate of 10 % into account, 146 subjects should be included in total.

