## Discussion

The current paper describes the rationale, design and methods of a cross-sectional study concerning participation in sports focused on children and adolescents with a physical disability or chronic disease.

To our knowledge this is the first study to evaluate this effect of sport participation on physical, social and mental health within this population. The aim is to determine both the positive and negative effects of sports related to health outcomes in children with disabilities and chronic childhood onset conditions. We hypothesize that the group participating in sports regularly will show higher levels of physical activity associated with better health outcomes, a relative lower incidence density, better cognitive functioning and school performance.

New insights gained from this study could stimulate the improvement of facilities for adapted sports by the government. Also children with a chronic disease or physical disability and their caregivers, sport coaches, physical therapists and other interested parties will be more easily convinced of the advantages of sports participation for this population.

Although we carefully chose our study settings according to its population, we are aware of some limitations of the study.

Objective measurements are chosen where possible. To achieve the best results possible, the best fitting testing modality will be chosen for each participant. The testing modality has to mimic the type of sport participated in. In children who do not participate in sport, the most common form of physical activity in daily life will be chosen as an indicator for the test modality. In general, some test modalities have been proven to elicit a higher VO_2_ peak in the same subject (Bhambhani et al. 1992). The test modality could therefore influence the test outcome. To minimalize this bias we will pursue a comparable number of testing modality types in both groups.

In conclusion, this study will provide insight in the effects of sports participation on the health of children and adolescents with a chronic disease or physical disability.

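### The one stated test rule does not fit injury density: on its natural reading it leads to a rank test that responds to hours of exposure as well as to injuries per hour

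*Protocol article*

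**What the plan says.** The injury endpoint is a rate. Under Injuries and illness: "The injury density (ID) will be calculated per 1000 h of scheduled physical activity". The Discussion states the hypothesis about it; the sport group is expected to show "a relative lower incidence density, better cognitive functioning and school performance".

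The abstract's Methods paragraph lists injuries among the outcomes compared between the groups and says that parametric and non-parametric statistics will be used. The Statistical analysis section then gives a single rule: "Data will be checked for normal distribution before applying the right type of parametric or non-parametric tests", followed by "Independent sample T-tests or appropriate non-parametric tests will be used" for sport versus non-sport. Injury density is not exempted, and no method that uses exposure hours is named.

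The abstract also defines the groups. Sport means organised sport twice weekly or more, kept up for three months or longer. That fixes a minimum number of sessions, not hours, but it makes more exposure in the sport group likely.

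**The concern.** A t-test or rank test needs one value per child, here injuries divided by hours. Such values are far from normal when many children have no injury, so the normality check points to the non-parametric branch. The usual two-group test there compares whole distributions. Two groups with the same injuries per hour but different hours do not have the same distribution of per-child densities, because the longer-exposed group has fewer zeros.

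The study aims to determine negative as well as positive effects of sport, and the Background describes parents and healthcare providers as wary of injury. A test that partly measures hours played could report a false harm per hour. It could also hide the lower density that the authors expect.

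**Working it through.** **Inputs from the article.** Density per 1000 h; a three-month retrospective window and one year of monitoring; alpha 0.05 and 66 per group ("with an alpha of 0.05 and bèta of 0.20 (power of 0.80) a sample size of 66 subjects per group is required"). The article gives no figure for the injury comparison, so there is none to reproduce. The 66 comes from peak oxygen uptake and is used here only as the group size. (The stated SD of 8.2 and a difference of 4.2, 10% of 42, give 2 × (1.960 + 0.842)² × 8.2² / 4.2² ≈ 60 per group. The stated 66 is larger, and this has no bearing on the point.)

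**Assumptions, not in the article.** Two-sided test; 1 to 10 injuries per 1000 h; weekly hours as shown, varying by ±30% between children; counts Poisson, or overdispersed (gamma frailty with variance 1).

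**By hand: 2 injuries per 1000 h in both groups, 52 weeks, 5 versus 2 h/week.**

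- Hours: 5 × 52 = 260 and 2 × 52 = 104.
- Probability of no injury: exp(−0.002 × 260) = 0.595 and exp(−0.002 × 104) = 0.812.
- Sport child injured, non-sport child not: 0.405 × 0.812 = 0.329.
- Non-sport child injured, sport child not: 0.595 × 0.188 = 0.112.
- Both injured: 0.405 × 0.188 = 0.076.

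Even if every both-injured pair is counted as non-sport higher, the sport child ranks higher in 0.329 of pairs against at most 0.112 + 0.076 = 0.188. Yet the mean density is 2 per 1000 h in both groups. Injured non-sport children have larger values, which balances the means, but ranks discard that size.

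If sport truly halves the density to 1 per 1000 h, its probability of no injury is exp(−0.001 × 260) = 0.771. So 22.9% of sport children are injured against 18.8% of the others, and the zeros still point the wrong way.

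**Simulation at equal density** (66 per group, 52 weeks, 2000 data sets per cell). Rank-test rejection, Poisson / overdispersed counts:

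| h/week | 1 per 1000 h | 2 | 5 | 10 |
|---|---|---|---|---|
| 5 v 5 | 5% / 5% | 5% / 5% | 5% / 4% | 5% / 5% |
| 3 v 2 | 9% / 8% | 9% / 9% | 7% / 9% | 7% / 7% |
| 5 v 2 | 41% / 33% | 44% / 38% | 26% / 28% | 12% / 15% |

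Repeat runs with other seeds gave 6–10% in the middle row and up to 18% in the last cell. The equal-hours row shows that the hours gap is the cause. With a two-fold or larger gap, 96–100% of rejections put the sport group higher; at a 1.5-fold gap most do. A robust rate-ratio test (total injuries over total hours) rejects in 4–7% throughout.

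**The route to the rank test.** Shapiro–Wilk rejected normality in at least one group in 99–100% of simulated data sets. The t-test on per-child densities stays at about 5–7% at 5 versus 2 h/week over one year, so the fault lies mainly in the rank branch.

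**Sport density truly halved, 52 weeks.** Share of trials concluding lower, Poisson / overdispersed; the rate is that of the non-sport group:

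| h/week, rate per 1000 h | Rank test | Rate ratio |
|---|---|---|
| 5 v 2, 2 | 2% / 2% | 48% / 41% |
| 5 v 2, 5 | 18% / 9% | 83% / 67% |
| 5 v 2, 10 | 77% / 26% | 98% / 82% |
| 3 v 2, 2 | 16% / 14% | 40% / 36% |
| 3 v 2, 5 | 50% / 30% | 77% / 61% |

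**Three-month window.** At 5 versus 2 h/week and equal density, the rank test rejects in about 13–45% across these rates.

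**The case against.** The article does not name a rank test. It says the right or appropriate test will be chosen, and it never says that density is computed per child. The density sentence also fits a group-level ratio. The section is three sentences of a condensed article, and the study is sized on peak oxygen uptake, so the model for one further outcome could reasonably sit in a fuller document.

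Part of this stands: the per-child rank test is inferred. But the point is not missing detail. A rule is stated, injuries fall under it, and a rate regression is neither a t-test nor a non-parametric test. On the group-level reading, the stated tests have no per-child values to work on, so the rule offers no test of the hypothesis.

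The size is also open to challenge, fairly. Scheduled physical activity need not mean only organised sport. If other scheduled activity counts in both groups, the hours ratio shrinks and most of the inflation goes. The density sentence sits with the three-month retrospective registration, and the article does not repeat it for the one-year monitoring. The one-year figures are therefore one scenario, though the fault appears in both windows.

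A reader might infer that the test would almost never show a truly lower density. That is not general: it does so in 50% of trials at 3 versus 2 h/week and 5 per 1000 h, and in 77% at 5 versus 2 h/week and 10 per 1000 h (Poisson counts).

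**Conclusion.** The concern holds in conditional form. On the natural reading (one density per child, many zeros, hence a rank test), the stated rule tests something other than the stated hypothesis. Where sport-group hours are higher, as the group definition makes likely, it rejects more often than 5% at equal density. It does so nearly always as sport worse when the gap is two-fold or more, and it loses power for a truly lower density.

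The one-year size with 66 per group runs from slight (about 6–9% at 3 versus 2 h/week) to serious (about 25–45% at 5 versus 2 h/week with 1–5 injuries per 1000 h, and 11–18% at 10 per 1000 h). These figures rest on assumed hours and rates, so the documents do not support quoting any one of them as the plan's error rate. Nor do they support saying that the plan prescribes a particular rank test. The mismatch between rule and hypothesis does not depend on the assumed figures. It should be corrected, but it does not touch the outcome on which the study is sized.

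**What to change.** Exempt injury incidence density from the normality-check, t-test and rank-test rule. Compare total injuries over total hours by Poisson or negative binomial regression of the count per child, with log(hours at risk) as offset and robust standard errors. Report the sport versus non-sport rate ratio with its 95% CI, and state which window it covers.

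The text change is a sentence or two, and one model replaces a simple test. The model needs each child's hours over the same window as the injuries. The article does not say that the fortnightly five-question form records hours, so it should not be assumed that no extra data are needed. A child with zero scheduled hours cannot enter the model, so the number of such children should be reported by group. With very few injuries, as in a three-month window at 1 per 1000 h, the robust test is conservative (about 2% or less under equal density), and the interval will be wide.

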## Design

The HAYS study will be a cross-sectional study comparing children and adolescents with a physical disability or chronic disease, age 10–19 years, who are actively participating in organized sports to their non-sporting peers. The subjects who participate in sports will be matched on gender, age and diagnosis to their non-sporting peers, Fig. 2.

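### The groups are matched on gender, age and diagnosis, but the named independent-sample tests ignore these factors; this costs precision and does not endanger the planned power

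*Protocol article*

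**What the plan says.** The Design section of the protocol article states: "The subjects who participate in sports will be matched on gender, age and diagnosis to their non-sporting peers". It gives no matching ratio or tolerance and does not say whether matching is subject by subject or by frequency.

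The Statistical analysis section is three sentences long: a normality check, descriptive statistics, and then "Independent sample T-tests or appropriate non-parametric tests will be used to to determine the differences between the sport and non-sport group". It names no pairing, stratification or covariate. The abstract describes the same plain two-group comparison.

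The Sample size section also treats the groups as unmatched. It takes the figure that "children and adolescents with cerebral palsy had an average peak oxygen uptake of 42 ± 8.2 ml/kg/min", aims "To prove a difference of 10 % between sporting or non-sporting subjects", and concludes that "a sample size of 66 subjects per group is required". It gives no within-pair correlation.

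**The concern.** The article states both the matching and the test, and they do not fit together. An analysis plan that handled the matching properly would have to depart from the article's text, so this is not a detail that an article merely leaves to a fuller document.

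Matching makes the two groups alike on the matching factors. Where these factors are related to an outcome, the outcomes of peers are positively correlated and the difference in means varies less than it would between two unrelated samples. An independent-sample test does not see this. It keeps the variation between ages, sexes and diagnoses in its standard error, so intervals are too wide and p-values too large. It also does nothing about age, gender or diagnosis differences that remain when matching is imperfect or a subject is lost.

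The study looks for negative as well as positive effects of sport, and an interval that is too wide can hide either. Only VO2peak was used to set the sample size, so precision matters for the other continuous outcomes too.

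**Working it through.** **Inputs from the Sample size section.** Mean 42 and SD 8.2 ml/kg/min; difference 10 %, taken as 0.10 × 42 = 4.2; alpha 0.05 (two-sided assumed, since the sidedness is not stated); power 0.80; 66 per group; 146 in total.

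**Input not in the documents.** The within-pair correlation ρ. It is an assumption, shown over 0 to 0.5.

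**The plan's own figure.** The unpaired formula gives n = 2 × (1.960 + 0.842)² × 8.2² / 4.2² ≈ 60 per group, or 61 with the exact t distribution. It does not give 66. The figure 66 appears if the difference is rounded to 4.0, or if 60 is multiplied by 1.10. That discrepancy is a separate matter. What counts here is that every one of these routes is an unpaired formula without a correlation term. The steps below take 66 as stated.

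**Formulas for 66 pairs.**

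1. Standard error used by the independent test: 8.2 × √(2/66) = 1.43.
2. True standard error of the difference under matching: 1.43 × √(1 − ρ). The interval is therefore too wide by the factor 1/√(1 − ρ). At ρ = 0.3 this is 1/√0.7 = 1.195, about 20 %.
3. True type I error: simulation of 20,000 data sets of 66 pairs with no group difference. The shortcut 2 × [1 − Φ(1.978/√(1 − ρ))] gives slightly lower values (0.048 at ρ = 0, 0.018 at ρ = 0.3), because it puts a t critical value into a normal tail.
4. Power of the independent test: Φ[(4.2/1.43 − 1.978)/√(1 − ρ)], confirmed by simulation.
5. Power of the matched analysis: paired t-test with SD of differences 8.2 × √(2(1 − ρ)). At ρ = 0.3 this SD is 9.70.

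| Assumed ρ | Interval too wide by | True type I error | Power, independent test | Power, matched analysis | Pairs for 80 % power |
|---|---|---|---|---|---|
| 0 | 0 % | 0.05 | 0.83 | 0.83 | 62 |
| 0.1 | 5 % | 0.04 | 0.85 | 0.86 | 56 |
| 0.2 | 12 % | 0.03 | 0.86 | 0.90 | 50 |
| 0.3 | 20 % | 0.02 | 0.87 | 0.93 | 44 |
| 0.5 | 41 % | 0.006 | 0.91 | 0.98 | 32 |

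**Frequency matching.** There are then no pairs. If the two groups have the same mix of ages, genders and diagnoses, the share of outcome variance explained by these factors takes the place of ρ in step 2. The direction of the error is the same.

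**Why not a plain paired t-test.** 146 subjects make 73 pairs. If 10 % of individuals fail independently, 0.9 × 0.9 = 0.81 of the pairs stay complete, about 59. A plain paired test would discard every remaining partner. Fifty-nine pairs cover the requirement at ρ = 0.1 (56) but not at ρ = 0 (62). A model that keeps single subjects avoids this loss.

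**The case against.** The strongest reply is that the error is on the safe side. With positive correlation the stated test rejects a true null less often than 5 %, and its power for VO2peak is 0.83 to 0.91 across the range, above the 0.80 planned. This stands. A reader might infer that the mismatch leaves the study underpowered or produces false positives, but the figures show neither. Ignoring a positive correlation also does not bias a difference in means.

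Second, a reader might take the Design section to mean one-to-one pairs. It does not say so, and the Sample size and Discussion sections speak at group level. The table is therefore an illustration for individual matching. This limits the figures but not the point: frequency matching calls for adjustment for the matching factors, and the named test does not provide that either.

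Third, ρ is undocumented and may be low for some of the many outcomes, such as attention or quality of life. At ρ = 0.1 the interval is only 5 % too wide. This stands, and it is why the range starts at 0. For physical measures at ages 10 to 19, across diagnoses from cardiovascular to neuromuscular, some positive correlation is the reasonable expectation, and it is the reason for matching at all.

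Fourth, one might conclude that broken matches bias the result. That would need losses that unbalance the groups, and nothing in the article shows that the 10 % failure rate differs between them. It is a possibility and not a demonstrated error. The choice between a t-test and a rank test after a normality check is a different question and adds no weight here.

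**Conclusion.** The point holds as a loss of precision: the named tests do not use the matching that the Design section sets up, whether that matching is individual or by frequency. At an assumed correlation of 0.3 the interval is about 20 % too wide, the true type I error is about 0.02, and power for VO2peak is about 0.87 where a matched analysis would give 0.93. At zero correlation nothing is lost. These sizes rest on 66 pairs, SD 8.2, a difference of 4.2 and a correlation that the documents do not give.

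The planned 80 % power for VO2peak is not endangered on this account. Any chance imbalance that remains in age, gender or diagnosis would go uncorrected; its size cannot be derived from the article. This should be fixed, but it does not invalidate the study.

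**What to change.** In the Statistical analysis section, replace the independent-sample test by one linear model per continuous outcome, with group, age, gender and diagnosis group as terms. Report the adjusted group difference with its 95 % confidence interval.

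State in the Design section whether matching is individual or by frequency, because the rest depends on it:

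- **Individual matching:** add matched set as a random effect, or use cluster-robust standard errors by matched set. Subjects whose peer is lost then stay in the analysis.
- **Frequency matching:** covariate adjustment alone suffices.

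Use test modality only in a sensitivity analysis. The Discussion section makes it depend partly on the sport practised, so routine adjustment could remove part of the contrast under study.

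The cost is one paragraph of text. Date of birth, gender and diagnosis are already collected in the general questionnaire. Individual matching also needs a matched-set identifier, which the article does not mention. The sample size need not rise on this account.

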## Discussion

The current paper describes the rationale, design and methods of a cross-sectional study concerning participation in sports focused on children and adolescents with a physical disability or chronic disease.

To our knowledge this is the first study to evaluate this effect of sport participation on physical, social and mental health within this population. The aim is to determine both the positive and negative effects of sports related to health outcomes in children with disabilities and chronic childhood onset conditions. We hypothesize that the group participating in sports regularly will show higher levels of physical activity associated with better health outcomes, a relative lower incidence density, better cognitive functioning and school performance.

New insights gained from this study could stimulate the improvement of facilities for adapted sports by the government. Also children with a chronic disease or physical disability and their caregivers, sport coaches, physical therapists and other interested parties will be more easily convinced of the advantages of sports participation for this population.

Although we carefully chose our study settings according to its population, we are aware of some limitations of the study.

Objective measurements are chosen where possible. To achieve the best results possible, the best fitting testing modality will be chosen for each participant. The testing modality has to mimic the type of sport participated in. In children who do not participate in sport, the most common form of physical activity in daily life will be chosen as an indicator for the test modality. In general, some test modalities have been proven to elicit a higher VO_2_ peak in the same subject (Bhambhani et al. 1992). The test modality could therefore influence the test outcome. To minimalize this bias we will pursue a comparable number of testing modality types in both groups.

In conclusion, this study will provide insight in the effects of sports participation on the health of children and adolescents with a chronic disease or physical disability.

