**Methods:**

In this cross-sectional study differences will be compared in regards to physical and psychosocial health, cognitive functioning, school performance, daily physical activity and injuries between children and adolescents with a chronic disease or physical disability who participate in sports and those who do not. Children and adolescents, both ambulatory and wheelchair dependent, in the age of 10–19 years with a physical disability or chronic disease will be included. “Sports” is defined as participation in an organized sport at least two times a week for a duration of 3 months or more prior to the assessment. Parametric and non-parametric statistics will be used to determine the differences between the two groups.

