### Participants

Eligible for this study are all children and adolescents aged from 10 up to 19 years with a physical chronic disease or condition, including cardiovascular, pulmonary, musculoskeletal, metabolic or neuromuscular disorders. Table 1 shows the in- and exclusion criteria. Both children who are ambulatory or those propelling a wheelchair are eligible for this study. Participants have to understand the Dutch language, understand simple instructions and be able to perform a physical fitness test. Children and adolescents in electric wheelchair, having a progressive disease or participate in other research projects which might influence the current study results will be excluded. Contra-indications for performing an exercise test, based on the exercise pre-participation screening questionnaire, may lead to exclusion on the cardiopulmonary exercise test (Balady et al. 1998).

**Table 1 Tab1:** Eligibility and exclusion criteria

Eligibility	Exclusion
Children and adolescents with a physical disability or chronic disease: cardiovascular, pulmonary, musculoskeletal or neuromuscular disorder Children and adolescents between the age of 10 and 19 years Children and adolescents have to understand simple instructions Children and adolescents are able to perform physical fitness tests	Children and adolescents with progressive diseases Children and adolescents using an electric wheelchair During the length of the study, children are not allowed to participate in other research projects which might influence the current study results For the sporting group of the HAYS-study only: subjects who have not participated in any sports for the preceding 3 months No signed informed consent

Informed consent must be provided by all parents, as well as by subjects up from 12 years till 17 years. In line with Dutch law, no parental informed consent is required for subjects aged 18 years and over.

This study was approved by the Medical Ethics Committee of the University Medical Center Utrecht, the Netherlands.

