#### Physical activity

Accelerometry in combination with heart rate monitoring will be used to measure the type, duration, frequency and intensity of physical activity in daily life. The Activ8 (2 M Engineering Ltd. Valkenswaard) will measure the modality of physical activity. The Activ8 system is new and has been recently be validated in cooperation with the Erasmus Medial Centre’s rehabilitation department in Rotterdam ([name] et al. work in progress). Participants who are able to walk wear one small sensor on the dominant leg. Participants in a wheelchair have to wear 2 small sensors (chest, one wrist). Participants will wear these monitors during the tests and during 7 days in their own environment. Wearing the activity monitor will not alter the activity pattern of the participants; all activities in daily life and in sport can be performed. The Actiheart (Camntech), will be used to detect the intensity of physical activity (Brage et al. 2005). The Actiheart is a small device detecting the heart rate frequency via two electrode-stickers on the chest and has been used previously in children with Spina Bifida (De Groot et al. 2013). During the 1 week of wearing the activity monitor, the participant will also fill out an activity diary in order to interpret missing data of the activity monitor. The completion of the activity diary will only take approximately 5 min per day.

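### The 7-day activity recording includes the organised sport that defines the sport group, so the comparison of total physical activity is partly circular and cannot show more activity outside sport

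*Protocol article*

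**What the plan says.** The Abstract (Methods) defines sports as "participation in an organized sport at least two times a week for a duration of 3 months or more prior to the assessment". The same section lists the outcomes on which the groups will be compared, among them "cognitive functioning, school performance, daily physical activity and injuries".

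The Physical activity section says that accelerometry and heart-rate monitoring are used "to measure the type, duration, frequency and intensity of physical activity in daily life". On the recording window it says: "Participants will wear these monitors during the tests and during 7 days in their own environment". The monitor is not taken off for sport: with it on, "all activities in daily life and in sport can be performed". For the diary, this section gives one purpose: "the participant will also fill out an activity diary in order to interpret missing data of the activity monitor". Table 3 also lists the diary next to the Activ8 as the instrument for type of activity. The general questionnaire collects type and frequency of sport.

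The Statistical analysis section compares the groups by independent-sample t-tests or non-parametric tests. The Discussion states the hypothesis that "the group participating in sports regularly will show higher levels of physical activity". Its one worked-out limitation is the exercise-test modality; it does not mention that the exposure overlaps with the activity outcome.

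**The concern.** The criterion that puts a child in the sport group is itself physical activity, and the outcome window will normally contain it. A group difference in total recorded activity has two parts: the sport sessions, and any difference in the rest of the week. The first part is expected from how the groups were formed. Only the second says whether sporting children are also more active otherwise, are the same, or rest more to compensate. The total does not separate them.

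The outcome is named daily physical activity, and the Discussion hopes the results will persuade government, caregivers and coaches. A higher total could easily be read as sport going together with a more active daily life in general. The planned comparison could give that impression even if the two groups behaved identically outside their sessions.

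**Working it through.** The article gives no effect size, SD, session length or active share for physical activity, so there is no stated figure to reproduce. The argument is structural; the arithmetic only shows how large the built-in part could be.

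**Structure.** Write total activity as S (organised sport) plus R (the rest of the week). The expected group difference in the total is (difference in S) + (difference in R). If the sport group keeps up its sport during the recorded week and the comparison group does none, the difference in S is positive. With R equal, the total differs in the hypothesised direction. If R is lower in the sport group by exactly the sport minutes, the total shows no difference. One observed total is therefore compatible with many values of R.

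**Inputs.**
- Sessions per week, k = 2: the minimum in the Abstract's definition.
- Group size, n = 66: the Sample size section, where it was derived for peak oxygen uptake, not activity.
- Session length L = 45 to 90 min, active share f = 0.3 to 0.8, between-child SD = 20 to 30 min/day: assumptions. Active minutes per day as the summary measure is also an assumption, since Table 3 lists only heart rate and type of activity.

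**Formulas.** Built-in difference m = k × L × f / 7 min/day. Standardised difference d = m / SD. Power of a two-sided 0.05 comparison by the normal approximation is about Φ(d × √(n/2) − 1.96), with √(66/2) = 5.745. R is taken as equal in the two groups.

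| L (min) | f | m (min/day) | d at SD 20 / 30 | power at SD 20 / 30 |
|---|---|---|---|---|
| 45 | 0.3 | 2 × 45 × 0.3 / 7 = 3.9 | 0.19 / 0.13 | 0.20 / 0.11 |
| 60 | 0.5 | 2 × 60 × 0.5 / 7 = 8.6 | 0.43 / 0.29 | 0.69 / 0.37 |
| 60 | 0.8 | 2 × 60 × 0.8 / 7 = 13.7 | 0.69 / 0.46 | 0.98 / 0.75 |
| 90 | 0.8 | 2 × 90 × 0.8 / 7 = 20.6 | 1.03 / 0.69 | 1.00 / 0.98 |

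With three sessions a week and the same ranges, m runs from 5.8 to 30.9 min/day and d from 0.19 to 1.54.

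**Reading.** With no difference at all outside sport, the chance of a significant difference in the total is above the nominal 0.05 in every row. It runs from about 1 in 10 to near certainty, depending wholly on values that the documents do not give.

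**The case against.** The strongest reply is that total activity is a legitimate outcome. The hypothesis speaks of levels of physical activity, not of activity outside sport, and the Physical activity section openly treats sport as part of what is recorded. The total also answers a real question: if sporting children rested enough to cancel their sessions, it would show no difference. This stands, and it is why the total should be kept.

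Three further points also stand in part.
- The qualifying sport lies before the assessment and the recording follows it, so sport in the recorded week is likely but not certain. Table 1 is looser than the Abstract: it excludes from the sporting group only "subjects who have not participated in any sports for the preceding 3 months", with no weekly frequency. Both weaken the overlap without removing it.
- The diary is not confined to missing data, because Table 3 also lists it for type of activity, and an analysis plan that is not shown may use it that way. However, the article does not say that session times are recorded, and times that were never collected cannot be recovered at analysis.
- Removing sport hours takes leisure time out of one group only, while the comparison group keeps its active play in those hours. A sport-excluded comparison is therefore not like for like and tilts against the sport group.

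A reader might go further and infer that the hypothesis is largely true by construction and bound to be confirmed. The documents do not support that. They give nothing from which to size the built-in part, the illustration includes trivial values, and compensation or unorganised activity in the comparison group could offset it. Nor does the article commit itself to reporting a higher total as a benefit for activity outside sport.

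**Conclusion.** The concern holds in a limited form. The recording takes in the sport that defines the group, the article states no separation of sport from non-sport time, and the overlap is not named as a limitation. The comparison of total activity is therefore partly circular, and a difference in it cannot be read as more activity outside sport.

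The direction is clear if other activity is equal: the built-in part favours the hypothesis. The size is not known. The range of 0.13 to 1.03 SD at two sessions a week rests entirely on the assumed session length, active share and SD, and on sport continuing through the recorded week. It would be equally wrong to say that the total is uninformative or that it should be dropped. This is an inexpensive improvement in what the study can conclude, and it has to be made before data collection.

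**What to change.** - Have the existing activity diary record the start and end of every organised sport session in the 7 days.
- Keep total activity as an outcome. Add a group comparison of activity outside organised sport, with those intervals removed from the Activ8 and Actiheart data and the remainder expressed per hour of remaining wear time.
- Base any statement about activity beyond sport on the second comparison, and present the two side by side.
- Add the overlap between exposure and outcome to the limitations in the Discussion.

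The cost is one diary field and one extra derivation, with no new measurement. The expected difference in the sport-excluded comparison is smaller. Because that comparison drops leisure hours from the sport group only, it should be read beside the total and not replace it.
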